## Abstract

**Background:**

Work and being able to work are important prerequisites for health and well being. Health problems can have a negative influence on the ability to work and not being able to work can be detrimental for patients’ psychosocial well being. Although GPs are aware of this importance they do not always structurally pay attention to patients’ work during their daily practice.

**Methods/design:**

To investigate whether GPs can be trained to increase their awareness of work and improve their skills when dealing with work related problems we designed a cluster randomised controlled trial. The intervention in this trial is a tailored training based on the findings of qualitative research with focus groups of GPs. Gender aspects received specific attention in these focus groups. Primary outcome measures are self efficacy of patients concerning return to work, and GPs’ use of ICPC code Z05 (work problems) and registration of patients’ occupation. Secondary outcome measures are work awareness of GPs as perceived by patients, quality of life, health, use of care and illness related costs. A process evaluation will be part of our study.

**Discussion:**

We investigate a training to increase work awareness among GPs, improve their skills in managing work related problems and structurally register work related data in the EMR. We think this study will make a contribution to better health care for workers by motivating GPs to appreciate their specific needs. It will also add to our knowledge of the complex relationship between gender, work and health.

**Trial registration:**

Trial registration number: NTR3475

## Background

Work, and being able to work, are important prerequisites for an individual’s health and well being [1]. For most people work means much more than just a source of income. Active participation in the community and making a valuable contribution lead to a higher self-esteem whereas not working often results in feelings of shame, isolation and loneliness together with their detrimental effects on health [2,3]. Although health professionals will understand the importance of their patient’s work, this is usually not reflected in the attention they pay to it in daily practice. Even general practitioners (GPs), who are trained to take into consideration the background and context of their patients, rarely pay attention to work-related health issues [4,5]. This neglect may result in patients who stay at home with minor illnesses or with chronic illnesses while both groups might be able to continue participation in their jobs after appropriate counselling by a health care professional. An important reason for the lack of attention for work-related health issues may be the fact that, unlike GPs in other countries, Dutch GPs do not have to certify sick leave [6]. This may also explain why there is a lack of research about this topic in the Netherlands and why the cooperation between GPs and occupational physicians has remained poor, despite many efforts to improve it [7].

Trying to enhance the work awareness of GPs is important, because GPs are usually the first health care professional contacted by workers with health problems, often long before these workers see an occupational physician (OP). Moreover they are generally highly trusted by the patients who explicitly prefer to be seen by their GPs during sickness absence [8]. Therefore GPs have an excellent position for early recognition and intervention of work related problems (WRP).

The lack of awareness in GPs for work problems may also be related to gender aspects. Work-related factors were found to influence the use of health care of male and female patients differently. Firstly, doctor-patient communication in general is strongly influenced by gender: male and female doctors act differently when confronted with similar problems [9,10]. Secondly, male and female patients differ in consultation behaviour. Women consult their GP more frequently and present more mental health problems [11]. Men consult less frequently, both as a result of cultural norms and practical hindrances like opening times of surgeries [12]. Men tend to identify more strongly with their jobs than women, who usually have more roles they identify with. Therefore the health consequences of losing a job can be more severe for men than for women [2]. Thirdly different factors have been shown to increase the risk for care-seeking in men and women. For men these are, for example, poor job satisfaction, routine work without opportunities for learning, physical load from bending forward and low demands in relation to competences [13,14]. For women these risk factors are, for example, reduced opportunities to acquire new knowledge, high physical loads, solitary work, and, especially for single mothers, the double burden of a job and the care of their families [2].

If work related problems are not addressed timely or properly this may contribute to long-term absenteeism from work or even to permanent disability [7]. To help medical professionals reduce the negative effects of unnecessarily lost working days, the Health Council of the Netherlands made recommendations about the management of diseases that frequently lead to long term absenteeism [15]. In its professional “Core Values” The Dutch College of General Practitioners recently addressed the importance of proactively paying attention to work [16]. Unfortunately this is not reflected yet in most of their guidelines [17].

There is limited evidence that GPs can be trained to improve their performance regarding sickness certification. Cohen et al. found an increased doctor reported self-efficacy among GPs in the UK after a tailored training [18,19]. Østerås et al. found that implementation of a structured functional assessment by Norwegian GPs influenced their prescription of part time and full time sick leave but had no effect on the duration of sick leave episodes [20]. Van Dijk et al. showed that the registration of risk factors for long-term sickness absence by Dutch GPs could be improved by using a protocol [21].

We conclude that there is a lack of attention of GPs to work-related health problems and that gender differences may play a role. We assume that education of GPs can increase their awareness of the possible two way relation - either causal or conditional - between work and presented health problems. This may lead to a better understanding of work-related problems and improve treatment strategies with benefits for both individual patients and society as a whole. Therefore we developed a GP education programme to increase GP awareness of work, also addressing the influence of gender of patients and GPs. The aim of this paper is to describe the design of a cluster randomised controlled trial about the cost-effectiveness of this programme. We will also evaluate the process of implementation.

## Methods

### Trial design

The study is a cluster randomised controlled trial using randomisation on practice level to prevent contamination. We will randomise the practices into two groups with a 1:1 allocation ratio. GPs in the intervention group practices will receive the training program, GPs in the control practices will deliver care as usual.

### Participants

#### General practitioners

GPs working in the South-Eastern part of the Netherlands will be asked by letter to participate in the study. If an insufficient number of GPs respond positively to the letter, GPs will be approached more directly by email and telephone. Only GPs who work at least 2 days per week will be recruited.

#### Patients

The patient population will exist of patients (from the lists of the participating GPs) who are 18–63 years of age, have paid work (paid-employment or self-employed) for at least 12 hours per week and have sufficient understanding of the Dutch language to fill in a questionnaire. The upper age limit of 63 was chosen to lower the chance that patients drop out during follow-up due to retirement.

### Randomisation

We aim to recruit at least 24 GPs who will be randomised into an intervention group and a control group. To prevent contamination, we will randomise clusters on practice level. A statistician will generate a block randomisation scheme using a block size of 2 and practices will be assigned to either condition according to the order in which they are recruited. After this order is established the allocation of the random sequence will be performed by the researcher.

### Intervention

We developed our intervention based on the literature and on the results of four focus groups with field experts of male and female GPs. This showed the importance of an active role of the GP [Qualitative article in progress]. Apart from lack of knowledge, for instance about legislation and gender, concern to become involved in a conflict between patient and employer turned out to be an important hindrance for GPs to address work. Therefore, the training has to stress the benefits of a proactive policy which entails coaching the patient to remain (or get) on speaking terms with the other relevant actors, thereby preventing or resolving conflicts. An accredited five hour training-intervention was developed to help GPs adjust their working style accordingly, covering the following items.

1. The connection between work and health (lecture).

2. Possibilities to improve usual care (discussion participants).

3. The rules regarding work and absenteeism and ways to come to a fruitful collaboration between GPs and OPs (lecture).

4. The gender aspects of work and work related problems (lecture).

5. Recommendations regarding a pro-active approach (lecture) and workshops about how to bring these recommendations into practice.

6. Advice regarding registration of work-related data in the electronic medical files (lecture)

7. Instructions regarding the data collection for the trial.

Two months after the initial training the participants will be offered a three hour booster training. Cases of the participants will be discussed with the researcher and the OP during the first part of these sessions. During the second part, consensus will be sought about feasible ways for GPs to structurally register work related data. These booster training sessions will be offered on two different days to optimise participation by intervention group GPs.

### Procedures

Inclusion will take place during a 4 month period, starting after the training of the intervention group GPs. The GPs’ receptionists will approach patients in the waiting room with a short questionnaire about age, number of working hours and their willingness to participate in the project. If a patient meets the selection criteria and signs informed consent the patient will be included and receive the first questionnaire. A second and third questionnaire will follow after 6 and 12 months. Forty patients for each participating GP, 20 females and 20 males, will be included for the study.

Only the intervention group GPs will be asked to fill in a form for each consenting patient with questions about: 1 the occupation of the patient; 2 the work relatedness of the problem that he/she presented; 3 whether sick leave was discussed; 4 whether the GP had suggested contacting an OP; 5 whether the GP had stimulated the patient to adopt a pro-active coping style. Two final questions asked whether the GP thought the training had been helpful for the consultation and if the GP had enough time for the consultation.

The control group will deliver care as usual. As it could be surmised that their usual care is influenced by the data collection we try to make sure that the data collection in the control group practices is carried out as much as possible by the receptionists supported by a research assistant. When data collection is completed the control group GPs are offered the same training as the intervention group as an incentive for adherence to the study protocol.

Patients will be approached by the receptionist before the consultation and, if they are prepared to participate in the study, are asked to answer the first questionnaire after the consultation and a second and third questionnaire after six and twelve months respectively.

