### Outcome measures

#### Primary outcome measures

As primary outcome measures at GP level we use the registration of patients’ employment in the electronic medical record (EMR) and the use GPs make of the code Z05 (for work related problems) of the International Classification of Primary Care (ICPC). For each participating GP we establish the percentage of the working age patients for whom the occupation is recorded anywhere in the EMR and we count the instances in which they made use of code Z05. The registration of employment and use of code Z05 in the 6 months following the training will be compared between intervention and control group practices.

The primary outcome measure at patient level is the work-related self-efficacy, measured by the 11 item Return-to-Work Self-Efficacy scale ( RTW-SE) [22]. This scale measures the extent to which people feel able to handle the demands of their job on a scale which ranges from 1 to 6. The RTW-SE is validated and reliable and has a high internal consistency. It was found to strongly correlate to return to work in a sample of sick listed workers; it was also shown to be sensitive to changes in the clinical condition of patients suffering from mental health problems [23].

Outcome measures regarding gender are the use of code Z05 and the registration of occupation in women and men. Moreover we will analyse the score on the RTW-SE scale and investigate its relation to gender and how this is modified by other patient variables like age, occupation, income, health problems, absenteeism and other patient variables.

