#### Secondary outcome measures

The secondary outcome measure at GP level is GP’s attention for the patients’ work related problems as it is perceived by patients. It is measured by a self-constructed five item scale, with 2 response categories: “yes” or “no” concerning: 1. Does the GP know your occupation? 2. Do you think the problem for which you consulted the GP is work related? 3. Was this possible relationship discussed by your GP? 4. Did your GP discuss sick leave? 5. Did the GP help you to find solutions for work-related problems?

As mentioned above, intervention group GPs are asked to fill in a form for each participating patient with questions on the same topics. This will provide us with information about the extent to which intervention group GPs and patients agree on these issues.

Secondary outcome measures at patient level consist of productivity, sick leave duration, health related to work, quality of life, self-rated health and direct illness-related costs, health care and non-health care. Measures for productivity are both absenteeism and presenteeism. Absenteeism refers to the total days lost from work. Presenteeism refers to attending work whilst still sick or disabled, causing reduced productivity while at work [22,24,25]. Sick leave and presenteeism will be measured with modules C and D of the Productivity and Disease Questionnaire (Prodisq) [26]. The Prodisq is developed based on the Quantity and Quality (QQ) method and provides a reliable and valid tool for measuring quantity and quality of work on a daily basis [25,26]. Quality of life will be measured by means of the RAND-36 and EQ-5D-5 L [27,28]. The RAND-36 consists of 8 subscales: physical functioning, role limitations due to physical problems, social functioning, bodily pain, general mental health, role limitations due to emotional problems, vitality, and general health perceptions [28]. The EQ-5D-5 L is an improved version of the Euroqol (EQ-5D). In contrast to the Euroqol, the EQ-5D-5 L has 5 levels of severity in 5 dimensions, instead of 3 levels of severity in 5 dimensions, which improves the instrument’s sensitivity [28].

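### A per-patient form completed only by intervention GPs may act as a reminder whose effect cannot be separated from that of the training

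*Protocol article*

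**What the plan says.** Procedures: "Only the intervention group GPs will be asked to fill in a form for each consenting patient". The first items are "1 the occupation of the patient; 2 the work relatedness of the problem that he/she presented; 3 whether sick leave was discussed". Two more ask whether the GP suggested the occupational physician and encouraged pro-active coping, and two process questions ask about the usefulness of the training and about consultation time. On timing, the same section says: "Inclusion will take place during a 4 month period, starting after the training of the intervention group GPs". It plans 40 patients per GP. It also accepts that data collection could alter usual care, and for that reason gives as much of the work as possible in control practices to receptionists and a research assistant.

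Primary outcome measures: the GP-level outcomes are the "percentage of the working age patients for whom the occupation is recorded anywhere in the EMR" and a Z05 count ("we count the instances in which they made use of code Z05"). The comparison is set as follows: "The registration of employment and use of code Z05 in the 6 months following the training will be compared between intervention and control group practices". For patients, "The primary outcome measure at patient level is the work-related self-efficacy", scored with the RTW-SE.

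Secondary outcome measures: after listing the five patient-rated attention items, the text notes that "intervention group GPs are asked to fill in a form for each participating patient with questions on the same topics". The purpose given is to see how far GP and patient agree.

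Effect evaluation: the main independent variable is whether the GP was trained or delivered usual care. The form is not named there, nor in Cost-effectiveness evaluation, nor among the weaknesses in Strengths and weaknesses of the study.

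**The concern.** A GP who knows that each enrolled patient brings a form on occupation and work-relatedness has a standing reason to raise those subjects. The training aims to produce the same behaviour, and the outcomes measure it. One arm has both influences and the other has neither. The precaution in the control practices keeps usual care clean, but it does nothing about the form in the intervention arm.

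What is at stake is attribution. The stated aim is to assess an education programme and its cost-effectiveness. If the form adds something, the trial estimates the effect of training plus form, while the programme costed and later rolled out may be training only. No analysis of the planned data can split the two afterwards, because every trained GP also has the forms.

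**Working it through.** **1. Amount of exposure.** Inputs: 40 patients per GP (Procedures) and 12 GPs per arm (Sample size). Intervention arm: 12 × 40 = 480 forms. Control arm: 0.

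**2. Timing.** Inclusion lasts 4 months and starts after the training, on an unstated date. The EMR window is the 6 months following the training. If inclusion starts within 6 − 4 = 2 months of the start of the window, all forms fall inside it; with a later start, some fall outside. The text therefore supports largely or wholly, not certainly all.

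**3. Overlap in content.** Occupation on the form matches the occupation outcome. Work-relatedness is the judgement that precedes a Z05 code. The plan itself says that the form and the attention scale share topics. The RTW-SE and the attention items are answered by the enrolled patients, so in principle every intervention patient analysed had a form.

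**4. Ceiling on the direct effect for occupation.** The denominator is all working-age patients of the GP. Its size is not given, so it is assumed. Ceiling = 40 / list size:

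| Working-age patients per GP (assumed) | Ceiling | If half were already recorded or would be recorded through training |
|---|---|---|
| 500 | 8.0 points | 4.0 points |
| 800 | 5.0 points | 2.5 points |
| 1,000 | 4.0 points | 2.0 points |
| 1,500 | 2.7 points | 1.3 points |
| 2,000 | 2.0 points | 1.0 point |

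Carry-over to patients who are not enrolled would add to this.

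**5. Z05.** If the form led to a code in 0 to 10% of form patients (assumption), that is 0 to 0.10 × 40 = 4 extra codes per GP. No baseline count is given, so the relative size is unknown. The Discussion says that even motivated GPs often do not know the relevant codes, which suggests a low base.

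**6. RTW-SE.** The plan's sample size comes first. Inputs: SD 1.14, difference 0.5 × 1.14 = 0.57, 80% power, alpha 0.05 (two-sided assumed), ICC 0.15, 30 analysed per GP, GP as the cluster.

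- Individual randomisation: 2 × (1.96 + 0.84)² × 1.14² / 0.57² gives 63 per arm.
- Design effect: 1 + (30 − 1) × 0.15 = 5.35.
- GPs per arm: 63 × 5.35 / 30 = 11.24, rounded up to 12. The plan's figure reproduces, with power of 82.6% (normal approximation) or 79.2% (t with 22 df).
- Recruitment: 30 / (1 − 0.25) = 40 per GP, as stated.

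Standard error of the arm difference: 1.14 × √(2 × 5.35 / 360) = 0.197 points. Suppose the training does nothing and the form alone shifts the RTW-SE by an assumed amount. The chance of p < 0.05 is then:

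| Assumed form effect | Chance of p < 0.05 |
|---|---|
| 0 | 5% |
| 0.1 SD (0.114 points) | about 9% |
| 0.2 SD (0.228 points) | about 21% |
| 0.3 SD (0.342 points) | about 41% |

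These rows show what would follow from an effect of each size. They are not evidence that such an effect exists.

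**The case against.** A reader might infer that the form is a second intervention in fact, and that a positive result would be due to it. The documents do not support that. Most items look back at what was done, a negative answer is acceptable, the form is not an EMR entry, and it does not ask for a Z05 code. A reminder effect is plausible, but nothing in the text shows or sizes one. The ceilings for occupation also overstate the form's own contribution, because the training and the booster session teach the same registration. For the RTW-SE, complete exposure is not a complete effect: the path from a GP's paperwork to a patient's self-efficacy is indirect.

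A reader might also infer that the randomised comparison is invalid. It is not. Read as a package, training plus form against usual care is a fair contrast. Nor is the form wholly detached from the programme: one training item covers instructions for trial data collection, and the form includes process questions. Giving controls the form would balance the arms but would prompt control care, which the plan reasonably wants to avoid.

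All of this stands, and it limits the point to attribution. It does not remove it. The plan presents the form as measurement, defines exposure as training, and offers controls the same training later with no mention of the form. Nowhere is a package declared.

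**Conclusion.** The point holds as one of attribution and should be fixed; it does not invalidate the trial. The asymmetry (about 480 forms against 0), the overlap in content and the one-sided precaution are all in the text. Timing inside the EMR window is largely or wholly established. A reminder effect of unknown size cannot be separated from the training effect.

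The consequence differs by outcome. For the occupation percentage the direct effect is probably small, with a ceiling of 2 to 8 points that rests on assumed list sizes of 2,000 to 500. For Z05 a few prompted codes could matter if use is low, but no baseline is given. For the RTW-SE and the attention items exposure is near complete, while the effect remains unknown. Saying that the trial cannot show that training works would go too far, because that would require a material form effect, which has not been shown.

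**What to change.** Choose one of two changes.

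(a) Have intervention GPs complete the form only for a small random subset of enrolled patients, revealed after the consultation. With 10 of 40, this gives 12 × 10 = 120 GP–patient pairs for the agreement question. It reduces prompting but does not abolish it, since the GP still knows that a form may follow. Outcomes with and without a form should not be compared within the arm: anticipation is the same for both groups, so the comparison would say little. The cost is less process data and a less precise agreement estimate, with a standard error up to √(480/120) = 2 times larger before clustering by GP is considered. GP workload falls.

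(b) If the form stays for all patients, define the intervention as training plus per-patient form in the aim, the exposure variable, the intervention costs and the conclusion, and list this as a limitation. The cost is a change of wording and a narrower claim.

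In either case, keep the all-patient EMR analysis as primary and add a sensitivity analysis that leaves enrolled patients out of numerator and denominator in both arms. It should not replace the primary analysis: patients consent after randomisation and after the GPs are trained, so enrolment may differ by arm and the exclusion could itself bias the comparison. It removes the direct form effect on the EMR outcomes but not carry-over to other patients, and it does not help the RTW-SE or the attention items. The cost is linking enrolled patients to their EMR records in every practice.
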